### Monitoring the participants

Participants will be contacted by post and phone as appropriate. In case of non-return of questionnaires, the participant will be sent a postal reminder or receive a telephone call.

### Data collection and processing

Follow-up will continue for six weeks from the date of operation. Clinical data will be collected on participants who will need to be followed-up in clinic, as part of their treatment plan.

Participants will be assessed pre-operatively to confirm eligibility and peri-operative data collected. Patient reported outcomes (PROs) will be collected by diary completed on days one to seven following surgery and by postal questionnaires at six weeks post-surgery. The components of participant follow-up are shown in the Table 1.

**Table 1 T1:** Source and timing of measures

**Outcome measures**	**Source**	**Timing**		
		**Peri- operative**	**Days one to seven diary**	**Six weeks**
BMI, ASA grade	Case Report Form (CRF)	▲		
Duration of operation, intra-operative complication rates, conversion rates, surgeon’s perception of single port approach	CRF	▲		
Intervention received	CRF	▲		
Body Image Questionnaire (BIQ) [20]	Participant Questionnaire (PQ)			▲
Hospital Experience Questionnaire (HEQ) [20]	PQ			▲
Pain Numerical Rating Scale (NRS)	PQ		▲	▲
Use of analgesics	CRF and PQ	▲	▲	▲
Time to return to usual activities	PQ			▲
Hospital re-admissions	CRF and PQ			▲
Complications (for example, infection, port-site hernia)	CRF and PQ	▲		▲

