#### Clinical outcomes

Analgesic use; duration of operation (minutes) and complication rates; conversion rates; infection rates (intra-abdominal and wound); related hospital re-admission rates up to six weeks; reoperation rates and port-site hernia up to six weeks.

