### Statistical analyses

For feasibility measures, such as the proportion of eligible patients who consent to randomisation, the frequency and corresponding 95% confidence interval will be calculated. Patient-reported and clinical measures will be summarised using appropriate summary measures (for example, frequency or mean and standard deviation) for each treatment group. The treatment groups will be compared at the two-sided 5% significance level. BIQ and pain NRS (area under the curve over a seven-day period) will be analysed using an independent *t*-test. Other outcomes will be assessed using standard statistical methods as appropriate, for example, comparison of proportions Newcombe’s CI method [21] or chi-squared test for trend [22], and independent *t*-test for binary and continuous outcomes respectively. Corresponding 95% confidence intervals will also be calculated. A single principal analysis is anticipated at the end of the study following intention to treat principle (grouped according to allocation). No imputation for missing data will be carried out. All analyses will be conducted using Stata 12 [23].

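### Collection of clinical data is tied to needing clinic follow-up, so six-week complications, re-admission, reoperation and hernia are not ascertained uniformly and the secondary clinical comparison is at risk of bias

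*Protocol article*

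**What the plan says.** All places are in the protocol article.

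- **Data collection and processing.** "Follow-up will continue for six weeks from the date of operation". The next sentence is "Clinical data will be collected on participants who will need to be followed-up in clinic, as part of their treatment plan". Patient-reported outcomes come from the diary and "by postal questionnaires at six weeks post-surgery".
- **Table 1, same section.** The row "Hospital re-admissions" and the complications row (infection and port-site hernia are its examples) both name the case report form and the participant questionnaire as sources at six weeks. Neither is restricted to clinic attenders. Reoperation has no row.
- **Clinical outcomes.** The list includes infection rates, and then "related hospital re-admission rates up to six weeks; reoperation rates and port-site hernia up to six weeks".
- **Monitoring the participants.** "In case of non-return of questionnaires, the participant will be sent a postal reminder or receive a telephone call".
- **Statistical analyses.** Groups are compared by allocation, and "No imputation for missing data will be carried out".
- **Abstract, Methods and design.** Clinical notes and operation notes are named as data sources beside the questionnaires.
- **Safety reporting sections.** Treatment-related serious events, including those that need re-admission or a prolonged stay, go on a separate form. Operating surgeons and theatre staff know the allocation.

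**The concern.** The sentence on clinical data makes collection depend on something that happens after randomisation and is probably related to the outcome: a patient with a wound problem is more likely to be seen again than one without. Clinician-confirmed six-week data would then be fuller for participants who fared badly. For the rest, the text states no six-week case report form or record check, although Table 1 implies that a form is completed.

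This matters in two ways. First, the event rates can be wrong in either direction, depending on how participants of unknown status are handled, and the trial is meant to inform the planning of a larger one. Second, if clinic review differs by arm, a difference can appear that reflects looking harder rather than worse results. That is plausible: the operating surgeons know the allocation, and the single-port technique is offered at this hospital only inside the trial, so closer review of that arm would not be surprising.

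**Working it through.** **1. The plan's own figures.** The protocol gives no complication rate, clinic-attendance rate or questionnaire return rate, so nothing on this point can be reproduced. Its power statement (effect size 0.65, 80 participants, two-sided 5%) concerns patient-reported measures. It checks out at 81.9% by a two-sample t-test with 40 per arm, and does not bear on this issue.

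**2. Which source covers whom at six weeks.**

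| Source | Covers | What it leaves open |
|---|---|---|
| Clinic data | Participants whose treatment plan needs a visit | Everyone else |
| Postal questionnaire, with reminder or call | All who return it | Non-returners; self-report is weak for hernia and for telling wound from intra-abdominal infection |
| Serious adverse event forms | Treatment-related events meeting a seriousness criterion, and all deaths | A minor infection or hernia managed as an outpatient may not qualify |
| Clinical and operation notes (Abstract) | Not restricted | No six-week review of every participant is stated |

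No row gives the same check to every randomised participant.

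**3. Effect on a single rate (all inputs assumed).** Let c = 15% be the true risk, r = 60–80% the questionnaire return, p1 = 60–80% the clinic review among those with an event, and p0 = 10–20% among those without. Return is taken as unrelated to the event and to clinic review, and status as correct once known.

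P(status known) = k = 1 − (1 − r)(1 − p), with p = p1 for k1 and p = p0 for k0.

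- Unknowns left out: c·k1 / [c·k1 + (1 − c)·k0].
  - Lowest (r = 0.8, p1 = 0.6, p0 = 0.2): k1 = 0.92, k0 = 0.84; 0.138 / (0.138 + 0.714) = 16.2%.
  - Highest (r = 0.6, p1 = 0.8, p0 = 0.1): k1 = 0.92, k0 = 0.64; 0.138 / (0.138 + 0.544) = 20.2%.
- Unknowns counted as event-free: c·k1 = 0.15 × 0.84 = 12.6% to 0.15 × 0.96 = 14.4%.
- Clinic data alone: c·p1 / [c·p1 + (1 − c)·p0], from 0.09 / (0.09 + 0.17) = 35% to 0.12 / (0.12 + 0.085) = 59%. The protocol does not plan this analysis; it shows how selected the clinic group could be.

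**4. Effect on the comparison when true rates are equal (assumed 10% in both arms).** Let d be the share of events found through clinic and s the share found by questionnaire. Observed rate = 0.10 × [1 − (1 − s)(1 − d)].

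| d in the two arms | s = 0 | s = 0.5 | s = 0.8 |
|---|---|---|---|
| 50% and 50% | 5.0% in both, ratio 1.00 | 7.5% in both, ratio 1.00 | 9.0% in both, ratio 1.00 |
| 30% and 50% | 3.0% and 5.0%, ratio 1.67 | 6.5% and 7.5%, ratio 1.15 | 8.6% and 9.0%, ratio 1.05 |
| 30% and 70% | 3.0% and 7.0%, ratio 2.33 | 6.5% and 8.5%, ratio 1.31 | 8.6% and 9.4%, ratio 1.09 |

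The ratios do not depend on the assumed 10%. Equal detection under-counts events but creates no difference. Unequal detection creates one, and the questionnaire shrinks it. In counts, with 80 / 2 = 40 per arm, the most extreme cell is 40 × 0.03 = 1.2 against 40 × 0.07 = 2.8 expected events.

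**5. Effect on the comparison when true rates differ (assumed 10% and 20%).** With r = 0.6, p1 = 0.8 and p0 = 0.1 in both arms, leaving unknowns out gives 0.092 / (0.092 + 0.576) = 13.8% and 0.184 / (0.184 + 0.512) = 26.4%, a difference of 12.7 points instead of 10. Counting unknowns as event-free gives 18.4% − 9.2% = 9.2 points. So ascertainment that is the same in both arms can still distort a risk difference.

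**The case against.** A reader might infer that six-week clinical data are collected *only* on clinic attenders and that the clinical comparison is therefore biased. The documents do not support either step.

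- The word *only* is not in the text. A fair reading is that no extra trial visits are imposed and that routine visits are captured when they occur.
- Other sources are stated: the questionnaire for complications and re-admissions, the chasing of non-returns, the clinical notes named in the Abstract, and the serious adverse event forms.
- No passage says that clinic review will differ by arm, or who decides on it. With equal true rates and equal detection, no false difference arises.
- A condensed article may leave the mechanics of completing a form to the full protocol.

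Most of this stands, and it removes any claim of demonstrated bias. What it does not remove is the wording itself. The article states a collection rule that depends on clinical course, sets it beside a table that implies collection for everyone, and lists reoperation as an outcome with no row in that table. That is a conflict in what is stated, not detail left out. The notes are named as a source, but nothing says that every participant's notes are checked at six weeks.

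**Conclusion.** The point holds as a risk to the secondary six-week clinical outcomes. Clinician-confirmed data would be uneven and linked to outcome, and the other sources reduce this without making ascertainment uniform.

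The size cannot be taken from the documents. On the assumed ranges, a true 15% would be reported as about 16.2% to 20% among participants of known status, or as 12.6% to 14.4% if unknowns count as event-free. With equal true rates, a spurious risk ratio of about 1.05 to 1.31 would need clinic detection to differ by 20 to 40 percentage points between arms while the questionnaire finds 50% to 80% of events. It would be larger if the questionnaire found none. In a trial of 80 this is a matter of one or two events.

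The two primary outcomes (body image at six weeks and the seven-day pain diary) and the peri-operative outcomes do not depend on clinic attendance. This is a modest weakness that is cheap to correct and worth correcting, because comparing clinical measures is a stated objective.

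**What to change.** Reconcile the sentence in Data collection and processing with Table 1. Suggested replacement: *At six weeks the hospital record of every randomised participant, whether or not a clinic visit took place, will be reviewed on the case report form for infection, re-admission, reoperation and port-site hernia.*

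Make this review the principal source for those outcomes, with all randomised participants as the denominator. Keep the questionnaire as a supplement for events managed outside hospital. Add a reoperation row to Table 1. It would also help to tabulate clinic attendance by arm, so that unequal review can be seen.

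The cost is about 80 case-note reviews by the existing team at the single recruiting hospital, plus the wording change. Clinic follow-up itself is unchanged. Two limits remain: events managed only by the GP still rest on the questionnaire, and a minor finding noted only because a visit took place will still be recorded more often in those who attend.

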### Outcome measures

#### Primary effectiveness outcomes

The patient reported outcome measure is the patient reported cosmesis and body image using the Body Image Questionnaire (BIQ) [20] at six weeks; participants will be asked five questions about their body image using the scale on a 4-point Likert scale of:’no, not at all’; ‘a little bit’; ‘quite a bit’; ‘yes, extremely’, two questions about their incisional scar to be rated on a scale of 1 (very unsatisfied/revolting) to 7 (very satisfied/beautiful), one further question regarding the scar using a 10-point Numerical Rating Scale (NRS), and a question regarding confidence on a 10-point numerical scale from 1 (not very confident) to 10 (very confident). The clinical outcome of severity of pain (Pain NRS) will be measured using a pain scale (scale from 0 (no pain) to 10 (worst imaginable pain)) at one to seven days.

#### Other patient-reported outcomes

Patient reported measures are the Hospital Experience Questionnaire (HEQ) [20] at six weeks where participants will be asked four questions about their experience in hospital (prior to the operation, treatment received, pain after operation and time to normal eating) to be rated subjectively using either a 4- or 5-level Likert scale (‘much too long’ to ‘much too short’; ‘very bad’ to ‘very good’; ‘no pain at all’ to ‘a lot of pain’; ‘no, not at all’ to ‘I cannot remember’) and one rating question on their view of the importance of different items (hospital stay, size of scar, no complications, pain after surgery, and resuming normal activities and diet). Additionally, any analgesic usage and time to return to normal activities will be collected.

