### Randomisation and allocation

Participants will be recruited from a single centre, Aberdeen Royal Infirmary (UK). Following consent and collection of baseline data, the local consultant/designated team member will randomise the patient.

Participants will be randomised to one of the two study groups in equal proportion using the randomisation application at the trial office at the Centre for Healthcare and Randomised Trials (CHaRT), Aberdeen. Randomisation will be stratified by gender and computer generated permuted blocks of varying size used within each stratum. This randomisation application will be available 24 hours a day, seven days a week as an Interactive Voice Response (IVR) telephone system. Due to the acute nature of the admission to surgery and potential difficulty in tracking patients, date of birth will also be recorded in the randomisation process and available, if necessary, for use in addition to the study number to identify patients. The date of birth will not be openly available.

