### Sample size

As there were no published RCTs comparing single port laparoscopic appendicectomy with standard three-port laparoscopic appendicectomy when the study was designed [8], a formal sample size calculation based upon previous data was not possible. A sample of 80 participants recruited is anticipated over the seven-month recruitment phase. Adopting a 5% two-sided significance level, this would allow an effect size (Cohen’s d) of 0.65 to be detected with 80% power for patient reported measures, such as the Body Image Questionnaire [19]. Binary feasibility measures are likely to be estimated with a (one-group) confidence interval of between 10 and 20% depending upon the corresponding event rate [19].

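### Time to return to usual activities is right-censored at six weeks, and the only method named for continuous outcomes (a t-test, without imputation) cannot use participants who have not yet returned

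*Protocol article*

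**What the plan says.** The Background lists faster recovery among the claims for single-incision surgery that lack evidence. The most direct measure of it is a secondary patient-reported item: "any analgesic usage and time to return to normal activities will be collected" (Other patient-reported outcomes).

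In Table 1 (Data collection and processing) the row "Time to return to usual activities" has the participant questionnaire as its only source and is marked only in the six-week column, not for the days 1-7 diary. The same section says "Follow-up will continue for six weeks from the date of operation".

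Statistical analyses assigns the independent t-test by name to BIQ and the seven-day pain AUC. Other outcomes are to be handled by suitable standard methods. The examples given are Newcombe's interval, the chi-squared test for trend and, for continuous outcomes, the independent t-test. The section adds "No imputation for missing data will be carried out" and defines intention to treat as grouping by allocation.

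The article names no time-to-event or rank method. It does not say how a participant who has not returned by six weeks is recorded, or what share is expected.

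**The concern.** A time asked about once, at the end of follow-up, is right-censored for anyone who has not yet had the event. Such a participant has supplied information (longer than six weeks) but no number. A t-test on observed times cannot use that information, and without imputation nothing takes its place. The participant is then left out because of the value of the outcome itself.

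At stake is the estimate of recovery. The comparison would be restricted to those who recovered within six weeks in each arm, and these subsets need not be comparable even though the arms were randomised. The Background also says the study should inform the choice and timing of outcomes for a larger trial, so a selectively truncated recovery estimate would carry over into that planning.

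**Working it through.** **1. The plan's own figure.** Inputs from Sample size: "A sample of 80 participants recruited is anticipated over the seven-month recruitment phase"; "Adopting a 5% two-sided significance level"; an effect size "of 0.65 to be detected with 80% power for patient reported measures, such as the Body Image Questionnaire". From Randomisation and allocation: "Participants will be randomised to one of the two study groups in equal proportion", so 40 per arm.

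- The noncentral t calculation for d = 0.65 needs 38.14, so 39 per arm (78 in total). With 40 per arm, power is 81.9%.
- The normal approximation gives 38 per arm (76) and 82.8% power.

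The statement reproduces. The present point does not depend on it.

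**2. Assumed inputs.** The article gives no recovery distribution, so these are assumptions: log-normal (log-SD 0.7) or exponential times; standard-arm median m = 7, 14 or 21 days; single-port median 0.7m; cut-off L = 42 days.

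**3. Formulas.**

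- Log-normal: P(T>L) = 1 − Φ(ln(L/m)/σ). Full mean = m·exp(σ²/2). Mean of those returned by L = full mean × Φ(ln(L/m)/σ − σ) / Φ(ln(L/m)/σ).
- Exponential: q = P(T>L) = 2^(−L/m). Full mean θ = m/ln 2. Mean of those returned by L = [θ − (L+θ)q]/(1−q).
- Loss = 1 − (difference with non-returners dropped)/(full difference).
- Restricted mean = mean of min(T, 42).

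**4. Worked case: log-normal, m = 21 v 14.7.**

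- Beyond day 42: 1 − Φ(0.990) = 16.1%, and 1 − Φ(1.500) = 6.7%.
- Full means: 21 × exp(0.245) = 26.83 and 14.7 × exp(0.245) = 18.78; difference 8.05 days.
- Means of those returned: 19.64 and 15.86; difference 3.78 days.
- Loss: 1 − 3.78/8.05 = 53%.
- Difference in restricted mean: 5.63 days.

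**5. Range (closed form, standard v single-port).**

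| Distribution, standard-arm median | Beyond day 42 | Full difference (days) | Dropped | Restricted mean | Loss v full | Loss v restricted mean |
|---|---|---|---|---|---|---|
| Log-normal, 7 | 0.5% v 0.1% | 2.68 | 2.50 | 2.63 | 7% | 5% |
| Log-normal, 14 | 5.8% v 1.9% | 5.37 | 3.65 | 4.63 | 32% | 21% |
| Log-normal, 21 | 16.1% v 6.7% | 8.05 | 3.78 | 5.63 | 53% | 33% |
| Exponential, 7 | 1.6% v 0.3% | 3.03 | 2.47 | 2.89 | 18% | 14% |
| Exponential, 14 | 12.5% v 5.1% | 6.06 | 2.33 | 4.26 | 62% | 45% |
| Exponential, 21 | 25.0% v 13.8% | 9.09 | 1.81 | 4.44 | 80% | 59% |

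The last column is the fairer benchmark for what six-week data can give, because no method recovers the full mean from follow-up that stops at day 42.

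**6. Power.** From 1,500 simulated trials of 40 per arm, the t-test with non-returners dropped is set against Mann-Whitney with non-returners as worst rank. For medians 7/14/21:

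- Log-normal: 51/48/40% against 58/59/60%.
- Exponential: 30/16/10% against 28/27/26%.

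The rank test gains nothing where almost everyone has recovered.

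**7. Direction.** A constructed case with 40 per arm:

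- Single-port: 36 at a mean of 12 days and 4 at 56 days, so (36×12 + 4×56)/40 = 16.4.
- Standard: 39 at a mean of 16 days and 1 at 56 days, so (39×16 + 56)/40 = 17.0.
- Full difference: 17.0 − 16.4 = 0.6 days.
- With late returners dropped: 16 − 12 = 4 days.

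Here exclusion enlarges the difference.

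**The case against.** **The t-test is not fixed for this outcome.** A reader might infer that it is. It is assigned by name only to BIQ and pain AUC. For the rest it is an example, and a survival or rank method would fall within the wording. This stands. But it is the only method offered for a continuous outcome, and none of the methods listed handles a censored time.

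**Dropping of non-returners is an inference.** No coding rule is given and the questionnaire is not shown, so it may already allow a not-yet-returned answer. The bar on imputation concerns missing data, and analysing a known censored time needs no imputation. This stands too. The point is therefore conditional: it bites if the stated default is applied to observed times.

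**A difference need not shrink.** A reader might infer that any recovery difference would. The constructed case shows it can grow when late recovery, for example after conversion or a complication, is commoner in the otherwise faster arm.

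**Intention to treat.** One might say the result would no longer follow it. The article defines the term as grouping by allocation, and incomplete outcomes do not change the grouping. That charge is not supported.

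**Size and importance.** The loss could be small if few remain unrecovered. Postal or telephone reminders (Monitoring the participants) may also let some returns just after day 42 be reported. Conversion, infection, re-admission and reoperation are separate outcomes, so a slower arm's complications would still be seen. All of this is fair and limits the weight of the point.

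**Conclusion.** The point holds in conditional form. The schedule right-censors this secondary outcome at six weeks, and the only method offered for continuous outcomes cannot use a participant known to exceed six weeks. Applied to observed times, it leaves participants out according to their outcome. The bias is usually towards zero but can run the other way.

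The size rests wholly on assumed distributions with a ratio of medians of 0.7. The loss in mean difference is about 7% with 0.5% of the slower arm not returned, and 53-80% with 16-25% not returned. Against the restricted mean, the losses for the same cases are 5% and 33-59%. No single figure in this range should be read as the expected loss.

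BIQ and pain AUC, the primary outcomes, are unaffected. The sample-size statement is sound.

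**What to change.** - Make sure the six-week questionnaire records that a participant has not yet returned to usual activities. An analysis plan cannot recover this later if the form does not ask.
- In Statistical analyses, state that such an answer is treated as censored at the questionnaire date, not as missing.
- Compare the arms by Kaplan-Meier curves with a log-rank test, or by the difference in restricted mean time to day 42, instead of the t-test. A rank test with non-returners as worst rank is an acceptable alternative.
- Report the proportion not returned by six weeks in each arm.

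The cost is at most one response option and one sentence. The downside is that the effect becomes a restricted mean difference, a hazard ratio or a rank comparison, not a plain difference in mean days.
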